**6.5 Analytical plan**

The analytical plan will be finalised before initiation of the analytical phase of the study.

# 7. ETHICAL AND ADMINISTRATIVE ISSUES

## 7.1 Ethics

This clinical study will be conducted in accordance with the principles laid down by the National Guidelines and the World Health Assembly of 1975 on Ethics in Human Experimentation and the Helsinki Declaration. This study will adhere to the standards established for Good Clinical Practices and conform to the TDR Standard Operating Procedures.

## 7.2 Ethical Committee Approval

Written approval to perform this trial will be obtained from the local Institution Review Board (AHRI/ALERT Ethical Clearance Committee), the Ethiopian and Nigerian National Ethical Clearance Committee and the WHO’s ERC , Geneva, Switzerland.

This amendment will be submitted and approval will be obtained from the Ethiopian and Nigerian National Ethical Clearance Committee and the WHO’s ERC, Geneva, Switzerland.

## 7.3 Informed consent

Each subject will receive detailed information (see informed consent form) and possible risks of the trial. This also includes information on HIV testing and counselling. Written informed consent will be obtained from every subject participating in the study. The subject will be at liberty to abstain from participation in the study and to withdraw consent at any time without compromising the regular treatment the subject is entitled to for his/her clinical condition.

## 7.4 HIV testing

All patients will be informed that they have the right to refuse HIV testing when it is offered. HIV testing will be mandatory for entry into the study. All patients who agree to HIV testing will receive pre- and post test counselling. The investigators will make every effort to offer voluntary testing and counselling and HIV testing to study participants so that VCT uptake is high. In addition, a serious attempt will be made to link subjects who are HIV positive to services that provide antiretroviral treatment where indicated.

## 7.5 Administrative matters

The Principal Investigator will prepare and maintain a file containing the essential documents for the conduct of a clinical trial as listed in the ICH Guidelines for Good Clinical Practices.

Patient records will be kept such that the identity of the patients will not be disclosed, and will be available for inspection by the clinical monitor and Study Director. CRFs of each study subject will be archived for 3 years. Arrangements will be made by the Sponsor so as to archive them for a longer period, as necessary.

Direct access to source data/documents relating to the trial should be granted to the sponsor for trial-related monitoring, audits, Ethical Committee review and regulatory inspections.

## 7.6 Reports and publications

The primary report of the study will be analysed by the WHO/TDR. It is agreed that publication of this study will be permitted, authorship to include all experts who have contributed to the development of this study, its analysis and interpretation. It is understood that there will be, prior to the submission of the manuscript, agreement on the data and their interpretation with the Study Director.

The Study Director/WHO will be free to use the data for the development of TB policy, on the understanding that on any such occasion there will be full and proper attribution to the source of the material and results. Such development or deployment may happen under the sole control of the WHO or in conjunction with the authorised partners of the WHO for the purpose of such development and/or deployment. The permission of the authors of the material will not need to be specially sought for such development or deployment. WHO will own the data but this will not in any way prevent the PI s from publishing the work.

## 7.7 Protocol Amendments

After the protocol has been signed, no changes may be made without the agreement of the PI, the Study Director and Sponsor. Any change will be signed and dated by all parties, attached to the original protocol and submitted for Ethical Committee review.

**Flow chart for MDR TB**

Week Zero

Intensive phase 2(HREZ)

Repeat sputum microscopy at

end of week eight

**If sputum smear negative** **If sputum smear positive**

Switch to continuation phase Continue with the intensive phase regimen until week12

Continuation phase (4HR daily regimen) Continuation phase (4HR daily regimen)

From end of week 8 to end of week 24 From end of week 12 to end of week 24

Repeat sputum smear microscopy

at week 20

If sputum smear negative If sputum smear positive

Send for culture and DST

Continue with 4HR until end week

24 **Exclude** from the study if Resistant to Isoniazid and Rifampicin-

For MDR-TB, refer to greenlight institution

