### ***Primary Outcome measures***

- cure rates at end of treatment (6 months). A cure is defined as one negative sputum culture in patients who did not fail treatment. A treatment failure is defined as:

1. a patient who is persistently smear positive by five months of treatment
2. a patient who becomes smear negative but positive again at or after five months of treatment (note: sputum positivity before this time is not considered a treatment failure)

- ***Secondary outcome measures***
- early response rates: proportion of patients with negative culture results at 8 weeks after initiation of therapy
- proportion of patients with relapses during the 72 weeks follow up period after the end of treatment. A relapse is a patient previously treated for tuberculosis who has met the case definition of cure (as defined above) and been declared cured by a physician and who has now been diagnosed with bacteriologically positive (two positive smears and culture positive) tuberculosis. If there is discordance between smear and culture results, a clinical decision will be made regarding further management: (i) smear positive, culture negative, and (ii) smear negative and culture positive.
- cure rates in HIV positive TB patients
- proportion of patients with clinical deterioration of pulmonary tuberculosis with the need for hospitalisation
- proportion of patients with *serious* adverse events any time during chemotherapy
- proportion of patients with any adverse events during chemotherapy
- proportion of patients completing treatment (defined as patients who achieved a total of 54 out of 56 doses in the first eight weeks of treatment AND 107 out of 112 doses at a daily rate during the subsequent 16 weeks of treatment) within each group. (96% doses taken considered as completed in intensive and maintenance phases).
- Proportion of patients who developed MDR-TB

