## 3.4 Treatment Regimens

### ***Study drugs:***

The drug regimens (see tables) will consist of 8 weeks of daily directly observed treatment (DOT) treatment, followed by 16 weeks of daily directly observed treatment. There will be two arms: (i) the intervention group - treatment will consist of 4FDCs (8weeks, i.e. **56 doses**) and 2FDCs (16 weeks, i.e. **112 doses**), and (ii) the comparator group - treatment with the same four and two drugs administered as loose formulations. The 4FDCs and the 2FDCs used will be identical across the different study sites, Nigeria and Ethiopia. Both 4FDCs and 2FDC preparations will include rifampicin. Full details of the drug regimen, including drug dosages, for each patient and of the procedure to be followed are given on the front and back of each Treatment Card.

The doses of drugs to be given to each patient are shown below and are based on the weight of the patient at the time of starting treatment.

*2. Weight between 40-54 kg (inclusive)*

*Intensive phase*.

For the patients allocated to the intervention regimen (FDCs) the dose for the first eight weeks of treatment is shown in the table below:

| MEDICATION  Combined tablet (COMB) of: | WEIGHT IN KILOGRAMMES |
| --- | --- |
|  | 40-54 |
| Ethambutol (275mg)  Rifampicin (150mg) Isoniazid (75mg) and  Pyrazinamide(400mg) | 3 tablets |

For patients allocated to the comparator regimen, the dose for the first eight weeks of treatment is shown in the table below:

| MEDICATION | WEIGHT IN KILOGRAMMES |
| --- | --- |
| as loose tablets (SEPA) | 40-54 |
| Ethambutol (400mg)  Rifampicin (450 mg)  Isoniazid (225mg)  Pyrazinamide (400 mg) | 2 tablets  1 tablet  1 tablet  3 tablets |

*Maintenance phase*.

For the maintenance phase, drugs will be administered under daily observation. The doses shown in the table below are based on the weight of the patient upon completion of the initial intensive phase:

| MEDICATION  Combined tablet (COMB) of: | WEIGHT IN KILOGRAMMES |
| --- | --- |
|  | 40-54 |
| Rifampicin (150mg)/Isoniazid (75mg) | 3 tablets |

For the comparator group, the regimen is shown below:

| MEDICATION  as loose tablets (SEPA) | WEIGHT IN KILOGRAMMES |
| --- | --- |
|  | 40-54 |
| Rifampicin (150 mg)  Isoniazid (225 mg) | 3 tablets  1 tablet |

*2. Weight between 55-70 kg (inclusive)*

*Intensive phase*.

For the patients allocated to the intervention regimen (FDCs) the dose for the first eight weeks of treatment is shown in the table below:

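### The flow chart extends the intensive phase to week 12 for week-8 smear-positive patients, contradicting the 8 + 16 week regimen in section 3.4 and leaving the completion outcome ambiguous for them

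*Protocol*

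**What the plan says.** Section 3.4 (Study drugs) states that the regimens "will consist of 8 weeks of daily directly observed treatment (DOT) treatment, followed by 16 weeks of daily directly observed treatment". For the intervention group it gives the dose counts: "treatment will consist of 4FDCs (8weeks, i.e. 56 doses) and 2FDCs (16 weeks, i.e. 112 doses". The comparator group receives the same drugs as loose tablets. The four-drug dose tables for both weight bands are headed as covering the first eight weeks. The visit schedule in section 3.6 labels week 8 as the end of the intensive phase and week 24 as the end of the continuation phase. None of these places makes an exception for a patient whose week-8 smear is positive.

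The flow chart for MDR TB splits patients on the week-8 smear. Smear-negative patients switch to the continuation phase. For smear-positive patients it says "Continue with the intensive phase regimen until week12", with continuation running "From end of week 12 to end of week 24". Both branches carry the same label, "Continuation phase (4HR daily regimen".

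The completion outcome (section 2.2, secondary outcome measures) has two parts. The first sets a threshold of 54/56 for weeks 1-8. The second, which must also be met, is worded "107 out of 112 doses at a daily rate during the subsequent 16 weeks of treatment". A closing parenthesis then describes the standard as 96% of doses and refers to the two treatment phases by name.

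**The concern.** The protocol describes two different regimens for the same patient. A dispenser working from section 3.4 and a clinician working from the flow chart would treat a week-8 smear-positive patient differently during weeks 9 to 12. If sites resolve the conflict in different ways, four-drug exposure varies by site for reasons unrelated to the comparison, and the regimen under test is no longer a single defined one.

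The completion outcome was written around 56 and 112 doses, which are the phase lengths in section 3.4. On the flow chart's longer path the phases are no longer 56 and 112 doses long. The outcome then means different things depending on whether doses are counted by calendar or by phase, and an adherent patient could be classed either way.

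**Working it through.** Inputs: daily dosing and the 8 + 16 week structure (section 3.4); the week-12 switch and week-24 end (flow chart); the thresholds 54/56 and 107/112 (section 2.2). Doses are weeks x 7.

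**The plan's own figures.** 8 x 7 = 56 and 16 x 7 = 112, total 168. Section 3.4 is reproduced exactly.

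**The flow chart branch for week-8 smear-positive patients.** The intensive phase is 12 x 7 = 84 doses and the continuation phase (weeks 13-24) is 12 x 7 = 84 doses, total 168.

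| | Section 3.4 | Flow chart, week-8 smear positive |
| --- | --- | --- |
| Four-drug doses | 56 | 84 |
| Two-drug doses | 112 | 84 |
| Total | 168 | 168 |

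Four-drug exposure: 84/56 = 1.5, so 50% more on the flow chart path. Treatment ends at week 24 on both.

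**The flow chart against itself.** The same continuation label stands over a 16-week branch (weeks 9-24) and a 12-week branch (weeks 13-24), so it cannot describe the length of both.

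**Completion thresholds.** 54/56 = 96.4% and 107/112 = 95.5%.

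**Completion for a fully adherent patient on the longer path, under each reading:**

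- By calendar window: weeks 1-8 give 56 of 56. Weeks 9-24 give 4 x 7 = 28 four-drug doses plus 84 two-drug doses, so 112 of 112. Both thresholds are met.
- By phase: at most 84 maintenance doses against 107 required (84/112 = 75% against 95.5%). The second threshold cannot be met.

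**Number of patients.** The week-8 smear-positive share is not stated. Purely as an assumption, 10% to 25% of the 498 per arm would be 0.10 x 498 = 49.8 to 0.25 x 498 = 124.5, or about 50 to 125 patients per arm. That range sizes how many would enter the longer branch, not how many would be misclassified; by calendar window none would be.

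**The case against.** The strongest reply is that the flow chart is simply a conditional branch on the default regimen, triggered by a smear that the schedule already requires, and that section 3.4 leaves full details to the Treatment Cards, which are not shown. The branch also applies alike in both arms and leaves the 6-month primary assessment where it was. Part of this stands: sites may have had a workable instruction on the cards. It does not cure the mismatch. Section 3.4 states its regimen without exception, its four-drug tables cover only eight weeks, the schedule ends the intensive phase at week 8, and section 3.6 collects the week-8 smear without giving it a treatment consequence.

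Three stronger readings are tempting and are not supported.

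- A reader might infer that the completion outcome is unattainable for patients on the longer path. The two dose clauses are worded as calendar windows and name no drug or phase, and on that wording an adherent patient passes. Only the closing parenthesis opens the phase reading, so the fault is ambiguity.
- A reader might infer that these patients drop out of the per-protocol set because of their week-8 response. Section 6.4 excludes patients who did not receive adequate chemotherapy but does not tie that to the completion rule. The loss would occur only if completion defined adequacy and were also counted by phase; the protocol states neither.
- A reader might see a further conflict in basing maintenance doses on weight at the end of the intensive phase. That instruction works on either path; its date follows the phase change.

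**Conclusion.** The regimen contradiction holds and needs correcting whatever is decided about the outcome. Section 3.4, its tables and the schedule give 56 + 112 doses; the flow chart gives week-8 smear-positive patients 84 + 84. The total is unchanged at 168, but four-drug exposure differs by 28 doses (50%).

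The completion point is secondary and narrower: for patients on the longer path the definition admits two readings, one that a fully adherent patient always meets and one that such a patient can never meet. Completion is a secondary outcome.

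The dose counts assume daily dosing through week 24, as both passages have it. The number of patients concerned cannot be derived from the protocol. No view is taken on which intensive-phase length is right.

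**What to change.** 1. Reconcile section 3.4, the headings of its dose tables, the visit schedule, the flow chart (including its continuation-phase label) and the Treatment Cards to one rule for patients who are smear-positive at week 8. Which rule is a clinical decision for the sponsor and investigators.
2. In the completion outcome, state that doses are counted by calendar window, weeks 1-8 and weeks 9-24, whatever phase the patient is in, and remove or reword the parenthesis that refers to phases. This works under either 24-week schedule. If reconciliation were to change the total length, the windows would have to be revisited.
3. Keep the stated counts of 54/56 and 107/112. Restating the rule as at least 96% would change it: 0.96 x 112 = 107.52, so 108 doses would be required, and a patient with exactly 107 would move from completer to non-completer.

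The cost is a protocol clarification, a check of the printed cards, and one sentence in the outcome definition. No new data are needed beyond the dose records already kept.

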**Recruitment flow chart**

**Suspected TB patient**

**Smear positive (2/3 or 2/5)**

**History/examination**

**HIV testing and counselling**

**Exclude if indicated**

**Inclusion and exclusion criteria**

**Exclude if indicated**

**Consent for trial entry**

**Further blood tests:**

**(FBC, EUC, LFT, Fasting BSL,**

**Urinary Pregnancy Test)**

**CD4 count if indicated**

**Exclude if indicated**

**Enrolment**

**Treatment allocation**

**Table 1. Recommendations for individuals with TB disease and HIV co-infection**

| CD4 cell count | Recommended regimen | Comments |
| --- | --- | --- |
| CD4 <200mm3 | Start TB treatment. Start ART as soon as TB treatment is tolerated (between 2 weeks and 2 months) a  EFV-containing regimensb, c, d. | Recommend ART.  - EFV is contraindicated in pregnant women or women of childbearing potential without effective contraception. |
| CD4 200−350/mm3 | **Start TB treatment.**  Start one of the regimens below after the initiation phase (start earlier if severely compromised):  EFV-containing regimens b  or NVP-containing regimens in case of rifampicin-free continuation phase TB treatment regimen. | **Consider ART.**  **Start ART after 8 weeks( after intensive phase) of TB treatment** |
| CD4 >350mm3 | Start TB treatment. | Defer ARTe |
| CD4 not available | Start TB treatment. | Consider ART a, f |

Adapted from WHO/HTM/HIV2004 - Scaling up antiretroviral therapy in resource-limited settings: Treatment guidelines for a public health approach - **2003** revision.

a Timing of ART initiation should be based on clinical judgement in relation to other signs of immunodeficiency. For extrapulmonary TB, ARVs should be started as soon as TB treatment is tolerated, irrespective of CD4 cell count.

b Alternatives to the EFV portion of the regimen include: Saquinavir/Ritonavir (SQV/r) (400/400 mg bid), SQV/r (1600/200 mg qd in sgc), Lopinavir/ Ritonavir (LPV/RTV) (400/400 mg bid) and Abacavir (ABC).

c Nevirapine (NVP) (200 mg qd for two weeks followed by 200 mg bid) may be used in place of Efavirenz (EFV) in absence of other options. NVP-containing regimens include: Stavudine/Lamivudine/ Nevirapine (d4T/3TC/NVP) or Zidovudine/Lamivudine/Nevirapine (ZDV/3TC/NVP).

d EFV-containing regimens include d4T/3TC/EFV and ZDV/3TC/EFV.

e Unless non-TB Stage IV conditions are present; otherwise start ARVs upon completion of TB treatment.

f If no other signs of immunodeficiency are present and patient is improving on TB treatment, ARVs should be started upon completion of TB treatment.

**Table 2. Guide for the management of patients presenting with TB before initiation of ART**

Guidelines for management of opportunistic infections and Anti retroviral treatment in adolescents and adults in Ethiopia, federal HIV/AIDS prevention and control office, FMOH, July 2007).

|  | **Recommendation** | **Preferred ARV regimen** |
| --- | --- | --- |
| CD4 count <200/mm3 | - Start TB treatment. - Start ART as soon as TB treatment is tolerated (usually between 2 -8 weeks of TB treatment)1 | EFV containing regimen is preferred.2 However, if drugs are not available or there are problems with EFV (adverse effects with intolerance and risk of pregnancy) NVP containing regimen may be given with caution, monitoring ALT every month (3). |
| CD4 count 200-350/mm3 | - Start TB treatment. - Start ART after 8 weeks (after intensive phase) of TB treatment | - Start NVP containing regimen if the continuation phase does not include Rifampicin. - Start EFV containing regimen if the continuation phase includes Rifampicin. |
| CD4 > 350/mm3 | - Start TB treatment - Defer ART | - Re-assess eligibility for ART at 8 weeks, in the course of TB-treatment, at completion of TB treatment, or as indicated. |
| CD4 not available | - Start TB treatment. - Start ART after 2-8 weeks of TB treatment | - Start NVP containing regimen if the continuation phase does not include Rifampicin. - Start EFV containing regimen if the continuation phase includes Rifampicin. |
| 1 Timing of ART initiation should be up to clinical judgment based on other signs of immunodeficiency indicating progression of HIV disease (Refer Table 1). For TB patients in WHO clinical Stage IV, ART should be started as soon as TB treatment is tolerated irrespective of CD4 cell count.  2 EFV containing regimens include d4T/3TC/EFV or ZDV/3TC/EFV.  3 NVP (200 mg daily for 2 weeks followed by 200 mg twice daily) may be used in place of EFV in absence of other options. NVP containing regimens include: d4T/3TC/NVP or ZDV/3TC/NVP.  5 Start ART if non-TB Stage IV conditions are present, re-assess the patient for ART at 8 weeks, during the course and at completion of TB treatment. | | |

